#### 2.5.3. Process Measures

At the screening and baseline visits, the following additional pieces of information are collected: general information, such as age, gender, date of birth, demographic and socioeconomic status; history of the disease, such as date of onset, date of management and etiology; medical and surgical history; analgesic treatments, concomitant medications and non-drug treatments; mapping of the thoraco-lumbar and lower limb painful areas; neuropathic pain assessment by clinician-administered diagnostic questionnaire (e.g., painDETECT Questionnaire (PD-Q)); and thoraco-lumbar MRI and brain imaging.

Patients who proceed to device implantation have the following information collected: mapping of the thoraco-lumbar and lower limb painful areas and paresthesia areas and recording of the various stimulation programs and stimulation parameters. The NeuroMapping tool is a validated quantitative tactile interface allowing the patient to delineate painful zones in the back and legs and to precisely map objective changes in pain coverage and SCS or DRGS performances [60,61].

Unscheduled patient visits could occur between scheduled study follow-up visits due to patient discontinuation from the study or device programming and management of any complication.

### 2.6. Procedures to Minimize Bias

To minimize selection bias, the randomization list will be prepared using the random selection program Ennov Clinical. Randomization numbers will be assigned in strict sequence; when a subject is confirmed as eligible for randomization, the next unassigned randomization number in sequence will be given. Randomization allocation will be concealed from the evaluator and subject, using a centralized automatic web-based data management system dedicated to the study and accessible to investigators by username and personal password (CS Online 7.5.10.11). Once assigned, the randomization assignment for the subject cannot be changed. Early departure from the study does not give rise to placement or reassignment of the rank of inclusion.

Due to the paresthesia generated by the TCS waveform, during the crossover period, patients will be under TCS waveform, whatever the type of stimulation. Consequently, patients will not be able to distinguish if they are under DRGS, SCS or DUAL stimulation. At the 3-month follow-up visit, all the patients will be switched to the burst waveform for a 1-month period while keeping the last allocated stimulation type in the randomized crossover arm. Patients will keep their stimulation in order to achieve optimal comparability between TCS and burst parameters.

To allow for investigator blinding, the evaluator will be different from the person who programs the IPG.

### 2.7. Statistical Analysis

#### 2.7.1. Sample Size and Power Calculations

In the ACCURATE study [24], the authors reported a significant difference between DRGS and conventional SCS for the treatment of the CRPS and causalgia using the following primary end point: “VAS decrease percentage ≥ 50% during lead trial and at 3-month follow-up and no incidence of neurological deficits due to stimulation”. They found that 81.2% of patients (56/69) responded to DRGS vs. 55.7% of patients (39/70) to SCS at 3-month follow-up. These data allowed us to estimate the necessary sample size that suffices to demonstrate a significant difference between the DRGS and conventional SCS. No data are available in the literature concerning DUAL stimulation. We estimate that DUAL stimulation superiority might arise from combining the effects of and mechanisms of action of both stimulation modalities.

With a level of significance at 0.05 and a power of 90%, we found that a number of patients set at 48 should be adequate to demonstrate a significant difference between the success proportions in SCS, DRG and DUAL stimulations in a six-arm crossover design.

Considering the possibility of a potential dropout (17%—lost to follow-up and possible explanted patients, which is the drop-out rate we observed in our previous studies [4,5]), and in order to have a sufficient number of patients allowing us to address secondary objectives, a total of 66 patients are planned to be included in the study.

#### 2.7.2. Main Statistical Analysis

Statistical analysis will be conducted using R software (Version 3.1.2, R Foundation for Statistical Computing, Vienna, Austria).

Data from phase A (12 patients) and phase B (54 patients) will be pooled (66 patients) for the main analysis.

Normality of distributions will be tested using the Shapiro–Wilk test. Either parametric or non-parametric methods will be used depending on the normality test results.

Our primary objective is to compare the efficacy of SCS, DRGS and DUAL stimulation at the crossover period based on the “50% VAS decrease” outcome.

Since our primary endpoint is a binary variable, we will use a mixed-effects logistic regression model, where the fixed effects are as follows: the treatment effect, the period effect and their interaction. The random effect is the random subject intercept. Fixed effects, their 95% confidence intervals and their significant level will be reported. Models will be estimated using restricted maximum likelihood estimation using the lmer function from the lmerTest package.

In case of significant effect of period and treatment, a two-step procedure will be conducted to assess pairwise differences between treatment effects. First, treatment effects will be estimated using a mixed-effects model as previously described, using data from each pair of treatments. Next, we will apply Holm–Bonferroni method to keep family-wise error under the 0.05 significance level.

In case the period effect is not significant, a Cochran Q test will be used to test the differences between the three groups. If the null hypothesis of the Cochran Q test is rejected, a McNemar test will be conducted for pairwise comparisons of the three groups. A Holm–Bonferroni correction will be applied to the *p*-values following the pairwise comparisons.

For the secondary outcomes, a two-factor repeated measure ANOVA (treatment + period factors) will be used to compare the continuous outcomes between the three treatments and a mixed effect logistic/multinomial regression model will be used to compare the categorical outcomes similarly to the analysis of the primary outcome. If the omnibus test’s *p*-value is significant, a pairwise comparison procedure with Holm–Bonferroni correction will be conducted.

At the 4-month period, the proportions of patients preferring the DRGS, the conventional SCS or the DUAL stimulation will be compared using a Chi-squared test.

Continuous outcomes at 4-month of burst DRGS, burst SCS and burst DUAL stimulations will be compared using an ANOVA or a Kruskal–Wallis test. In case the ANOVA (or Kruskal–Wallis test) is significant, a pairwise comparison will then be conducted using independent *t*-test or Mann–Whitney test depending on the variable distribution. A Holm–Bonferroni correction will be applied on the pairwise comparison.

The categorical outcomes will be compared using a Chi-squared test or an exact Fisher test when the Chi-squared assumptions are not met. A generalized mixed-effects model with a patient specific random intercept will be used to estimate the global treatment effect including the 6-month and 12-month follow-ups. The link function used in the model will depend on the type of the studied outcome (logistic or multinomial for categorical outcomes and no link function for continuous outcome).

The relationship between performance (percentage of pain covered with stimulation) and “induced” pain relief (global pain VAS) will be estimated by Kendall’s tau and its 95% confidence interval. The correlation between selectivity (percentage of paresthesia covering pain) and paresthesia discomfort will also be estimated using Kendall’s tau.

Mean energy consumption will be compared between the different types of stimulation using repeated measures ANOVA or a Friedman test.

Tonic stimulation will be compared to burst stimulation using patient last crossover stimulation modality. The comparison will be conducted using a paired *t*-test or a Wilcoxon signed-rank test using data from the last crossover period compared to the 4-month data using burst stimulation. VAS decrease will be compared between all the SCS modalities at 6-month and 12-month follow-ups using a two-factor ANOVA (preferred anatomical target x preferred stimulation type).

A sub-analysis of the sample will be conducted in order to assess the effect of burst waveform on the brain signals visualized using brain imaging data with and without burst stimulation.

Two interim analyses are planned. The first interim analysis will be conducted on data from the first 12 patients included (after the “Tonic” crossover period). In this first interim analysis, we will analyze only the safety criteria, the objective being to assess study feasibility. The second interim analysis will be conducted on data from the first 33 patients included (after the “Tonic” crossover period) and will be exclusively descriptive. No hypothesis testing will be conducted. This analysis will be conducted on primary and secondary outcomes. As the study is of long duration (3.5 years), we decided to include a second interim analysis to communicate the results to the scientific community by clearly indicating that this is an interim analysis and that the final analysis will be conducted on the total sample of 66 patients. This may lead to other projects and accelerate the progress of research on the stimulation of several anatomical targets. These results will have no impact on study completion. The final analysis on 66 patients will be considered for the report and the publications.

Only data from the crossover period will be used in the interim analysis. The statistical methods used in this interim analysis will be similar to the methods used in final analysis described above. No adjustment of the final analysis *p*-values will be conducted as the interim analysis results do not influence in any way the course or the conduct of the study.

A significance level of 0.05 will be considered in this study (after taking into account multiple testing corrections) and all tests will be two-sided.

All the analyses will be conducted based on an Intention-To-Treat (ITT) principle using complete cases. No missing data imputation will be conducted. An initial safety analysis will be conducted on the first 12 patients to assess the initial safety of implementing patients with both DRG and SCS stimulations. A final safety analysis will be conducted on the 66 patients. Frequencies of adverse events and deviations from protocol will be compared between the treatments following an ITT analysis.

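### A normality pretest may choose the method for the continuous secondary outcomes and so displace the period-adjusted crossover model that the plan names

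*Protocol article*

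**What the plan says.** All of this stands in the protocol article, section 2.7.2.

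- The general rule: "Normality of distributions will be tested using the Shapiro–Wilk test", followed by "Either parametric or non-parametric methods will be used depending on the normality test results".
- The primary endpoint: "Since our primary endpoint is a binary variable, we will use a mixed-effects logistic regression model". A normality rule has no bearing on it.
- The continuous crossover outcomes: "a two-factor repeated measure ANOVA (treatment + period factors) will be used to compare the continuous outcomes between the three treatments". No rank alternative is given at that point.
- Energy consumption: "Mean energy consumption will be compared between the different types of stimulation using repeated measures ANOVA or a Friedman test". This is the only place where Friedman appears, and the ANOVA named beside it is not said to contain period.
- The between-group comparison under burst: "Continuous outcomes at 4-month of burst DRGS, burst SCS and burst DUAL stimulations will be compared using an ANOVA or a Kruskal–Wallis test". The tonic-versus-burst comparison is likewise given two options, a paired t-test or a Wilcoxon signed-rank test.
- The level: "A significance level of 0.05 will be considered in this study (after taking into account multiple testing corrections) and all tests will be two-sided".

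Section 2.5.2 defines the secondary outcomes as changes from baseline. Section 3.5 concedes that there is no wash-out and that carryover cannot be ruled out.

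**The concern.** Two statements in one section pull apart. One fixes a model with treatment and period for the continuous crossover outcomes. The other lets a pretest decide between parametric and non-parametric methods, without limiting where it applies. If the general rule prevails, a continuous crossover outcome that fails Shapiro–Wilk needs a rank test for three repeated conditions, and Friedman is the only one in the plan. Friedman ranks within patients and cannot adjust for period, although the plan puts period into both its primary and its secondary crossover models.

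Two consequences follow. First, outcomes of one family could be tested under different hypotheses (means, or within-patient ranks), with or without period adjustment, as decided after the data are seen. Second, the pretest may look at the wrong thing. ANOVA needs well-behaved residuals after the patient effect is removed. A test of the outcome values themselves can reject because patients differ from one another in a skewed way, although the within-patient comparison is sound.

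**Working it through.** **What the plan supplies.** It gives no SD, effect size, correlation or power for any continuous outcome, so there is no figure of its own to reproduce on this point. The 48 patients in section 2.7.1 are for the binary primary endpoint. Usable inputs are 66 patients, 17% dropout, six equal sequences, three periods and two-sided 0.05. Completers: 66 × (1 − 0.17) = 54.8, about 55.

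**Efficiency of Friedman.** For k conditions and normal errors, efficiency relative to ANOVA is (3/π) × k/(k + 1). With k = 3 this is 0.955 × 0.75 = 0.72. Without any period effect, 55 patients analysed by Friedman are worth about 55 × 0.72 = 39.

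**Simulation, all inputs assumed.** Between-patient SD is 1.0 and within-patient SD 0.7, so the within-patient correlation is 1/(1 + 0.49) = 0.67. There are 48 to 66 patients, and effects are set to give ANOVA power of 80% or 90%. Total period drift is 0, 0.4 or 0.7 (0, 0.57 or 1.0 within-patient SD). The two-stage rule was taken as follows: Shapiro–Wilk p < 0.05 in any of the three period samples leads to Friedman, otherwise ANOVA with patient, period and treatment.

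*Friedman used always, normal within-patient errors, 80% base power:* the loss is 14–16 points with no drift, 16–19 with drift 0.4 and 24–29 with drift 0.7.

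*The two-stage rule itself, 55 patients, 80% base power, drift 0.7, normal within-patient errors:*

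| Between-patient values | ANOVA with period | Friedman always | Two-stage rule | Switch to Friedman | Residuals rejected |
|---|---|---|---|---|---|
| Normal | 80.1% | 56.1% | 76.9% | 14% | 2% |
| Skewed (lognormal) | 79.8% | 55.1% | 58.7% | 85% | 4% |

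The loss is 80.1 − 76.9 = 3.2 points in the first row and 79.8 − 58.7 = 21.1 in the second. Switch rate times the always-Friedman loss gives nearly the same: 0.14 × 24.0 = 3.4 and 0.85 × 24.7 = 21.0. The 14% switch rate under full normality is about what three separate 5% tests produce: 1 − 0.95³ = 14.3%.

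*Two-stage rule across all settings run:* it loses 2–5 points when all components are normal (switch in 13–14% of trials). It loses 9–25 points when the patient component is skewed (switch in 80–90% of trials), although residuals are rejected in only 2–5%. A second simulation with 54 patients and about 82% ANOVA power gave 3–4 and 11–21 points. With skewed within-patient errors it ran from a 3-point gain to a 5-point loss.

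*Type I error, 54 patients, no treatment effect:* the two-stage rule rejects in 5.2–5.3% of trials without drift and in 3.0–4.4% with drift 0.7. ANOVA stays at 4.6–5.2%.

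**The case against.** The strongest objection is that the plan does not send the continuous crossover outcomes to Friedman. For those outcomes it names one method, which includes period. Where it means to allow a switch, it writes out both options: ANOVA or Kruskal–Wallis, paired t-test or Wilcoxon, repeated-measures ANOVA or Friedman. On that reading the general sentence governs only the listed pairs. Even for energy consumption no period term is dropped, because none is stated. This stands as a fair reading. The other reading is equally open, because the general sentence carries no limit, so the text needs settling either way.

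A reader might infer that the plan gives up 14 points of power or more on every continuous crossover outcome. The documents do not support that. Such figures describe Friedman used always, under normal within-patient errors, with effects and drifts that the plan does not give. Under the two-stage rule the loss depends on how often the pretest rejects. Where skewness is strong the switch can be neutral or helpful. In one simulated pain-surface scenario the switch occurred in over 99% of trials, yet raw-scale ANOVA had 56% power and Friedman 57%. With lognormal within-patient errors and no or modest drift, Friedman used always gained up to 10 points.

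A reader might also infer false-positive inflation, and none is shown. Nor does the plan say outright that raw values are tested. It leaves the object of the test open, and the full analysis plan may specify it.

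**Conclusion.** The point holds as an unresolved conflict within section 2.7.2 and an avoidable data-driven choice of method. It is limited to the continuous secondary outcomes. Whether the general rule overrides the period-adjusted ANOVA cannot be decided from the text. If it does, the named fallback omits period.

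The cost is conditional. At around 80–90% ANOVA power and 48–66 patients, the two-stage rule loses about 2–5 points if all components are normal, and about 9–25 if patients differ in a skewed way while residuals are normal. With skewed within-patient errors it moves a few points in either direction. These ranges rest on assumed SDs, effects and drifts, a 0.05 pretest level, and the test being applied to outcome values in each period. The case for change rests mainly on having one hypothesis per outcome fixed in advance. The power figures show that keeping the period-adjusted model generally costs little and can save a good deal.

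**What to change.** Delete the Shapiro–Wilk switch. For every continuous crossover outcome, energy consumption included, fix in advance a linear mixed model with treatment and period as fixed effects and a random patient effect. Judge the fit on residuals, not on raw values. Report robust or bootstrap confidence intervals, and keep a rank-based analysis as a sensitivity analysis only.

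If a transformation is wanted for pain surface or energy, apply it to the post-treatment value with baseline as a covariate, and state how zeros are handled. Do not log the change scores that section 2.5.2 defines, since they can be zero or negative. For the month-4 comparison between groups and the tonic-versus-burst comparison, name one test per outcome.

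The cost is wording only. There are two drawbacks: a small loss of power where within-patient errors are strongly skewed and period effects are small, and reporting log-transformed results as ratios.

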### 3.5. Study Limitations

Despite potential interest, this study has several limitations. First, as mentioned above, the comparison between TCS (involving a paresthetic effect) versus burst (a paresthesia-free modality) will not be performed under strict and homogeneous blinded conditions, by sequentially testing the different stimulation modalities. However, burst will be applied for the three groups (SCS, DGRS and DUAL) between the 3rd and the 4th month after randomization, which will allow for the comparison of paresthesia-free conditions as a second step, in a second phase. This should not interfere with our main endpoint, at 3-month follow-up, involving TCS and paresthesia for each group of stimulation, in a strict double-blind manner. Second, this crossover design will not allow us to determine long-term efficacy of each stimulation modality, since multiplying the number of modalities to evaluate implies proportionally decreasing the length of the follow-up period for financial and ethical reasons. An alternative point of view would counterbalance this loss of potential valuable information with the fact that this design can also be considered as “added value” for the patient, who will be able to choose his preferred spatial target and waveform, thereby enhancing treatment adherence. Following this perspective, we will collect maximal follow-up for the stimulation modality, which will reflect the patient’s preference. Third, the absence of wash-out period will not allow us to claim that one modality could not induce a carryover effect. However, the 1-month period used for each modality should cancel out this potential carryover effect. Fourth, mechanisms of actions will be assessed at the supraspinal level, even though some modulations can occur at the spinal level. In their in vitro simulation study, Zannou et al. [74,75] interestingly reported tissue heating when stimulation was applied at a high-frequency modality, which that may impact more or less long-term clinical outcomes. Realistic anatomical computational models of SCS are crucial tools and provide opportunities to better understand the role of complex tissue compartments in shunting the current applied to the potential neural targets [74,75,76].

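### The treatment-by-period interaction in the primary model and the switch of test on period significance leave the reported treatment effect and the test to a weak pre-test; one additive model would remove both

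*Protocol article*

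**What the plan says.** Section 2.7.2 of the protocol article sets out the primary analysis in this order:

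- A mixed-effects logistic regression for the binary 50% VAS reduction, with a random patient intercept, "where the fixed effects are as follows: the treatment effect, the period effect and their interaction". The fixed effects, their confidence intervals and significance are to be reported. Estimation is by REML with lmer.
- If period and treatment are both significant, the same kind of model is refitted to the data of each pair of treatments, with Holm–Bonferroni adjustment.
- Otherwise: "In case the period effect is not significant, a Cochran Q test will be used to test the differences between the three groups". McNemar tests with Holm–Bonferroni adjustment follow.

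The section does not say how treatment is tested while the interaction is in the model, whether effects are averaged over periods, or what follows from a significant interaction. For continuous secondary outcomes it uses treatment and period factors only.

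Section 3.5 concedes that there is no wash-out and argues that "the 1-month period used for each modality should cancel out this potential carryover effect".

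**The concern.** With three treatments and three periods, the interaction gives each of the nine treatment-by-period cells its own parameter. A treatment coefficient from such a model need not be the treatment effect averaged over the trial. Under reference coding it is the effect in the reference period, which rests mainly on comparisons between different patients. The precision that justifies a crossover is then largely missing from that coefficient, and sparse cells can make logistic coefficients run to infinity.

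The period test also decides which analysis follows. Depending on a p-value for a nuisance factor, the pairwise result comes either from interaction models or from McNemar tests that ignore period. These are different tests and can estimate different quantities.

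**Working it through.** **Inputs.** Section 2.7.1 gives the response rates: "They found that 81.2% of patients (56/69) responded to DRGS vs. 55.7% of patients (39/70) to SCS at 3-month follow-up". On the third arm it says "No data are available in the literature concerning DUAL stimulation", so the DUAL rate is assumed to lie between 81.2% and 90%. No within-patient correlation is given; ICC 0.1 to 0.7 is assumed on the linear scale, and a random-intercept SD of 1.0 on the logit scale. Section 2.1 gives six equal sequences. Each treatment-by-period cell occurs in two of the six, so 48 patients give 48/3 = 16 per cell. The planned 66 with 17% dropout give 66 × 0.83 = 54.8, or about 18 per cell; 66 with no dropout give 22.

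**1. The plan's own figure.** Section 2.7.1 reads "With a level of significance at 0.05 and a power of 90" per cent, then "we found that a number of patients set at 48 should be adequate"; section 2.7.2 adds that "all tests will be two-sided". A paired McNemar calculation for 81.2% vs 55.7% needs 72, 59, 53, 46 and 40 patients at within-patient correlation 0, 0.2, 0.3, 0.4 and 0.5. Simulated Cochran Q at 48 patients (DUAL 81.2%) has 81%, 89% and 93% power at latent correlation 0, 0.3 and 0.5. A logistic mixed model with treatment and period only has 90.3%. So 48 is reproducible for a fully within-patient analysis with moderate correlation. Independent groups would need 69 per arm.

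**2. Variance of the reported effect.** Set the within-patient residual variance to 1, with N = 48.

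- Additive model: variance of DRGS minus SCS = 2/48 = 0.0417.
- Parallel comparison of 16 vs 16 in period 1: 2/[16 × (1 − ICC)].
- Interaction model, period 1 as reference: generalised least squares for the six-sequence design.

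| ICC | Interaction, period 1 | Ratio to additive | Parallel 16 vs 16 | Share of parallel variance | Ratio in pairwise refit |
|---|---|---|---|---|---|
| 0.1 | 0.1369 | 3.29 | 0.1389 | 99% | 3.32 |
| 0.3 | 0.1576 | 3.78 | 0.1786 | 88% | 4.06 |
| 0.5 | 0.1750 | 4.20 | 0.2500 | 70% | 5.00 |
| 0.7 | 0.1898 | 4.56 | 0.4167 | 46% | 6.23 |

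Averaged over periods, the interaction model gives a ratio of 1.00. The loss therefore comes from reading a single-period coefficient, not from fitting the interaction as such.

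A contrast with 90% power has expected z = 1.96 + 1.28 = 3.24. Dividing by √3.32 = 1.82 gives 1.78, or about 43% power; dividing by √5.00 = 2.24 gives 1.45, or about 30%. Both are before Holm adjustment.

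**3. Sparse cells (logistic fit).** With m patients per cell and three cells per treatment, treating cells as independent:

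P(at least one cell all responders or all non-responders) = 1 − ∏ over treatments of [1 − pᵐ − (1 − p)ᵐ]³.

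At m = 16, 0.812¹⁶ ≈ 0.035 and 0.9¹⁶ ≈ 0.185.

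| Per cell | DUAL 81.2% | DUAL 90% |
|---|---|---|
| 16 | 20% | 52% |
| 18 | 13% | 43% |
| 22 | 6% | 29% |

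Simulation with correlated responses at 16 per cell and no period effect gave 18% and 50%, in agreement.

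**4. The period pre-test.** N = 48, no treatment difference. In the additive model, drifts totalling 0.8, 1.0 and 1.5 logits over the three periods are detected in about 27%, 40% and 67% of trials. For the 1.0-logit drift, the reference-coded interaction model detects it in 17%, because the coefficient then describes period in one treatment only.

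**5. The whole procedure.** Simulation at N = 48, DUAL 81.2%, no period effect, 1,300 runs. The treatment terms read at period 1 have 39.5% power, against 90.3% in the additive model. With the switch included, omnibus power is 87.4% when the interaction model with reference coding feeds it and 89.7% when the additive model does: 2.3 points lower. Type I error of the switch fed by the additive model was 5.1% to 5.4% (4,000 runs per setting); with the reference-coded interaction it was 6.1% to 7.2% (1,300 runs).

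**The case against.** The strongest reply is that the period-1 reading requires a coding choice the article does not make. Its talk of significant period and treatment effects, and of an omnibus p-value for secondary outcomes, fits factor-level tests, and contrast coding is ordinary material for an analysis plan. That stands: the variance ratios and the 39.5% are conditional on reference coding. But the article also says the fixed effects themselves will be reported, which leaves that reading open, and the interaction and the switch are stated choices.

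Second, a reader might infer that the trial as a whole gives up its within-patient precision, or that the primary comparison is in effect 16 vs 16, with power of about 33%. The document supports neither. When period is not significant, Cochran Q and McNemar are fully within-patient, and without drift this branch is used in most trials. No 16 vs 16 test is planned.

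Third, a reader might infer that the primary model will often fail outright. An infinite coefficient does not disable a likelihood-ratio omnibus test or the Cochran and McNemar branch. The problem arises only in a logistic fit. As literally named, lmer with REML fits a linear model, where it does not occur; that mismatch with the logistic model is a separate matter. The upper percentages also need a 90% DUAL rate.

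Finally, the wash-out remark in section 3.5 concerns carryover and is no evidence about coding, sparse cells or the switch. Examining treatment by period is reasonable when there is no wash-out; the question is whether it belongs in the primary model.

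**Conclusion.** The point holds in limited form and should be fixed. As written, the reported treatment effect and the pairwise test depend on a period test that detects a 1.0-logit drift in about 17% to 40% of trials. The harm falls on the reported effects and on pairwise inference when period is significant. There, under reference coding, variances are about 3.3 to 5.0 times the additive ones at ICC 0.1 to 0.5, and in a logistic fit individual coefficients can diverge in about 13% to 43% of trials at 18 per cell. The effect on the omnibus decision is small, about 2 points of power.

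It would be wrong to conclude that the switch by itself materially inflates type I error, or that the crossover's advantage is lost in general. The sizes rest on an assumed DUAL rate, assumed correlations and, for the variance figures, reference coding with period 1 as reference.

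**What to change.** Pre-specify one logistic mixed model with treatment, period and a random patient intercept, to be used whatever the period p-value. Take the 2-df treatment test and the three Holm-adjusted pairwise contrasts from that single fit. Delete the period-significance branch. Move treatment by period, or a first-order carryover term (estimable with six sequences), to a sensitivity analysis, and keep Cochran Q and McNemar as supportive checks.

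This matches the treatment and period structure already planned for continuous secondary outcomes. The cost is wording and two degrees of freedom always spent on period. With six balanced sequences period is orthogonal to treatment, so the additive term costs almost no precision. No change to sample size or data collection is needed.
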